**Methods:**

The MINIMUM study is a prospective, randomized, controlled, single center enrolling 200 patients scheduled for open pancreatoduodenectomy comparing the microdialysis method to the “standard of care.” Half of the included patients will be randomized to receive an intraperitoneal microdialysis catheter implanted at the end of surgery and will be monitored by microdialysis as an additional monitoring tool. The other half of the patients will not receive a microdialysis catheter and will be monitored according to the current standard of care. The primary objective is to evaluate if the microdialysis method can reduce the total length of stay at the hospital. Secondary endpoints are the frequency of complications, length of stay at the hospital at our institution, catheter malfunction, number of infections and bleeding episodes caused by the microdialysis catheter, patient-reported quality of life and pain, and cost per patient undergoing pancreatoduodenectomy. The patients will be randomized in a 1:1 ratio.

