Secondary 4	To evaluate the reliability and complications using microdialysis catheter CMA 65	Occurrence of catheter malfunction Occurrence of bleedings and infections	Daily check of the microdialysis catheter is functioning. Assessments of bleeding which affects circulatory parameter (development of circulatory shock or need of transfusion) and infection
Secondary 5	To evaluate patient quality of life and pain	Overall score and sub-scale scores of patient-reported questionnaires	Two patient-reported questionnaires: “Abdominal surgery impact scale” will be gathered with patient-reported McGill Pain Questionnaire-2 (SF-MPQ-2) preoperatively, at POD3 ± 1 day and at discharge ± 2 days from primary hospital + 30 and 90 days after surgery.
Secondary 6	To compare hospital costs of using microdialysisis versus “standard of care”	Number of Euros per patient undergoing PD based on microdialysis costs, length of stay (ICU and inpatient stay), reoperations, and postoperative complications	From medical records, procedures noted in electronic patient records, and radiological electronic patient records.
Exploratory	To compare other endpoints between patient with and without a microdialysis catheter	Hours from end of surgery to diagnosis of postoperative pancreatic AL (grades B and C).	Time as noted in electronic patient records.
		Total quantity (μg/mg) of vasoactive medications during surgery	Amount during surgery where the PD was performed. Derived from electronic patient records.
		Fluid balance - total iv volume administered and total diuresis	Diuresis and amount of fluid given iv during surgery and postoperatively until discharge from the hospital where the PD was performed. Derived from electronic patient records.
		Number of patients with biliary fistula	Biliary fistula defined according to the definition of the International Study Group of Liver Surgery (ISGLS). Graded into A, B, or C. From medical record, CT-scans.
		Number of patients with gastro-enteric AL	Gastro-enteric AL. From medical record, CT-scans.
		Pancreatic amylase and bilirubin concentrations in drainage fluid and in serum.	Analysis of drainage fluid and serum
		White blood cell count, C-reactive protein; concentrations	Laboratory data
		Number of patients with postoperative complications during total hospital stay in total and per complication	Defined by the modified Clavien-Dindo classification, from medical record, radiological examinations, and electronic patient records.

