**Table Taba:** 

Efficacy	Power	Sample size per group
-1 day(s)	0.818	155
-1 day(s)	0.909	202
-1.5 day(s)	0.814	58
-1.5 day(s)	0.932	84

In the MINIMUM study, we assume a reduction in total hospital stay ~ 1.5 days. With a significance of 0.05 and a power of 0.93, we will randomize 100 patients in each group considering that ~ 15% of the patients will not have a pancreaticoduodenectomy performed. If this number appears to be higher than the first estimate, the sample size needs to be recalculated.

The statistical analysis plan will be developed and finalized before database lock and will describe the participant populations to be included in the analyses, along with procedures for the accounting of missing, unused, and spurious data. The statistical analysis plan will be developed partly using blinded data to check for assumptions. Blinding is obtained by exchanging the treatment variable with a random allocation variable prior to any results. No unblinded analyses will be performed prior to the finalization of the statistical report. The primary endpoint will be analyzed using a log-logistic regression model with the treatment group as covariate. Results from the model will be presented as the difference in median time in hospital LOS, with 95% confidence intervals. Deaths will be imputed with worst outcome. Secondary dichotomous endpoints will be analyzed using logistic regression with the treatment group as covariate. Results from the model will be presented as odds ratios with 95% confidence intervals. Missing data will be imputed with worst outcome. Secondary continuous endpoints will be analyzed using linear regression for non-repeated measures or mixed effects linear regression for repeated measures. Generalized linear model versions or quantile regression models will be considered if the assumptions underlying the normal linear model are assumed to be violated based on blinded analyses. Treatment differences will be presented with 95% confidence intervals. Time to event endpoints will be analyzed using competing risk methodology, with the event and death as competing risks. Results from the model will be presented as hazard ratios with 95% confidence intervals.

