### Criteria for premature termination of a patient’s participation in the trial

Consent withdrawal or in the case of the surgery ending without a pancreatoduodenectomy being performed will be considered a termination of the patient’s participation in MINIMUM. A malfunction of the microdialysis catheter or analysis equipment will make it impossible to achieve further adequate microdialysis data. The patients will be followed until discharge and follow-up appointments at 30th and 90th POD, irrespective of a malfunctioning catheter or not.

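### Coding missing secondary binary endpoints as the worst outcome biases the odds ratios: towards 1 if missingness is balanced, in an unpredictable direction if it is not

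*Protocol article*

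**What the plan says.** The section Statistical considerations of the protocol article gives the model for binary secondary endpoints, "Secondary dichotomous endpoints will be analyzed using logistic regression with the treatment group as covariate", then the effect measure, "Results from the model will be presented as odds ratios with 95% confidence intervals", and directly after that the rule "Missing data will be imputed with worst outcome". By its position the rule belongs to the dichotomous secondary endpoints. It names no arm and makes no exception for safety outcomes.

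Table 1 lists "Occurrence of bleedings and infections" under Secondary 4. Bleeding is assessed there as bleeding with a circulatory effect (shock or transfusion), and infection without further restriction, so both can occur in either arm. Fistula is the endpoint of Secondary 1 and becomes dichotomous if analysed as yes or no. The Interim analyses section uses haemorrhage and infections, with deaths, as its safety data.

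The same statistical section says that the statistical analysis plan will describe how missing data are accounted for. No expected missing rate is given for any binary endpoint. The only loss figure is that about "15% of the patients will not have a pancreaticoduodenectomy performed".

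**The concern.** Worst-outcome coding is usually defended as conservative. That defence fits a one-arm success rate. It does not fit a between-arm comparison of harms. If the same fraction is missing in both arms, the rule adds non-observed events to both, and the odds ratio shrinks towards 1. For an implanted device added to standard care, this is the direction in which a real increase in bleeding or infection is harder to see. A real benefit, such as fewer fistulas, is diluted in the same way.

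If the missing fractions differ, the rule adds more events to one arm than to the other, and the result depends on who had missing data. The trial is open-label and catheter patients are sampled far more often, so equal missingness cannot be taken for granted. Finally, a single imputed value enters the regression as if it had been observed, so the confidence interval carries no allowance for the imputation.

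**Working it through.** **The plan's own numbers.** The sample-size table gives 84 per group at power 0.932 for a 1.5-day reduction. Allowing for about 15% without the operation: 84 / (1 − 0.15) = 98.8, that is 99. The plan states "With a significance of 0.05 and a power of 0.93, we will randomize 100 patients in each group", so its figure is reproduced. Evaluable patients are then 100 × 0.85 = 85 per arm, used below. Allocation is 1:1.

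**Assumptions.** Event rates and missing fractions are not in the article and are assumed. Missingness is taken as unrelated to outcome, and tests as two-sided at 0.05.

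**Effect of the rule.** With true rate p and missing fraction m, the analysed rate is p′ = p(1 − m) + m. With equal m in both arms and true odds o₁ and o₀, this gives OR′ = (o₁ + m) / (o₀ + m), which always lies nearer 1 than o₁ / o₀.

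Balanced missingness, true 15% v 5% (OR 0.1765 / 0.0526 = 3.35), 85 per arm:

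| Missing, each arm | Analysed rates | OR | Power under the rule | Power, observed data only |
|---|---|---|---|---|
| 0% | 15% v 5% | 3.35 | 0.59 | 0.59 |
| 1% | 15.85% v 5.95% | 2.98 | 0.55 | 0.58 |
| 2% | 16.7% v 6.9% | 2.71 | 0.51 | 0.58 |
| 5% | 19.25% v 9.75% | 2.21 | 0.42 | 0.56 |
| 10% | 23.5% v 14.5% | 1.81 | 0.32 | 0.54 |

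Power = Φ[(d − 1.96 × SE₀) / SE₁], where d is the difference in rates, SE₀ uses the pooled rate and SE₁ the separate rates. At 10% missing:

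- Under the rule (n = 85): d = 0.09, SE₀ = 0.0602, SE₁ = 0.0598, giving Φ(−0.47) = 0.32.
- Observed data (n = 85 × 0.9 = 76.5): d = 0.10, SE₀ = 0.0485, SE₁ = 0.0478, giving Φ(0.10) = 0.54. The odds ratio stays at 3.35.

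A rarer outcome suffers as much: true 9% v 3% (OR 3.20) becomes 2.33 at 2% missing, 1.84 at 5% and 1.52 at 10%.

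**Uncertainty.** The standard error of the log odds ratio is √[1/(n₁p₁(1−p₁)) + 1/(n₀p₀(1−p₀))]. At 10% missing it is √(1/9.75 + 1/3.63) = 0.61 on observed data and √(1/15.28 + 1/10.54) = 0.40 under the rule. The rule gives a tighter interval around a biased value.

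**Unbalanced missingness** (intervention v control):

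| True rates (OR) | Missing | OR under the rule |
|---|---|---|
| 20% v 10% (2.25) | 15% v 5% | 2.77, exaggerated |
| 20% v 10% (2.25) | 5% v 15% | 1.03, hidden |
| 20% v 10% (2.25) | 0% v 15% | 0.81, reversed |
| 10% v 10% (1.00) | 10% v 5% | 1.38, created |
| 5% v 5% (1.00) | 10% v 3% | 1.99, created |

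**Patients without the operation.** The article says that "surgery ending without a pancreatoduodenectomy being performed will be considered a termination" of participation. If these roughly 15% were nevertheless kept in the analysis set with their missing outcomes coded as events, m would be about 0.15 and the OR of 3.35 would become (0.1765 + 0.15) / (0.0526 + 0.15) = 1.61.

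**The case against.** The strongest reply is that little may be missing. Bleeding with shock or transfusion is recorded in hospital, and fistula comes from the medical record and CT. The research team sees patients daily and telephones them at 30 and 90 days, and the monitor pursues queries on missing entries until they are resolved. This stands: at 1% to 2% missing, the distortion in the main example is from 3.35 to 2.98 or 2.71. Large missingness would require keeping the patients without pancreatoduodenectomy. The article ends their participation, sizes the trial to absorb their loss, and leaves analysis populations to the statistical analysis plan.

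A second reply is that missing-data procedures are deferred to that plan. This stands in part. Sensitivity analyses may be there, so a reader who infers that none is planned goes further than the article allows. But the general deferral does not withdraw a rule the protocol has already fixed.

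Three stronger readings are tempting and not supported:

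- That the odds ratio always moves towards 1. This holds only for balanced missingness, as the second table shows. Application to both arms is the natural reading, but it is not stated.
- That the rule hides harm caused by the catheter. Controls have no catheter, so catheter-caused events (the abstract's wording) and catheter malfunction cannot occur in them, and a between-arm odds ratio has no meaning. Within the intervention arm the rule would inflate these rates. The dilution argument applies to bleeding and infection of any cause, as Table 1 assesses them.
- That power falls from 0.59 to 0.32. The 0.59 needs complete data. The fair comparison at 10% missing is 0.54 against 0.32. Even 0.59 is low for a threefold rate, so these comparisons are weak in any case.

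**Conclusion.** The concern holds in limited form. As written, the rule biases between-arm odds ratios for binary secondary endpoints and understates their uncertainty. The bias is towards 1 when missingness is balanced and can take any direction when it is not. Its size depends on event and missing rates that the article does not give. In the main example it is modest at 1% to 2% missing, and at 10% it takes the odds ratio from 3.35 to 1.81. The primary length-of-stay analysis is not touched by this rule. It is a cheap improvement to secondary analyses, of modest severity.

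**What to change.** In the statistical analysis plan, before database lock:

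1. Make the main analysis of dichotomous secondary endpoints either an observed-data analysis or multiple imputation from baseline and in-hospital data.
2. Keep worst-outcome coding in both arms as a sensitivity analysis. For harms, add a version that codes missing values as events in the intervention arm and as non-events in the control arm.
3. Report catheter-caused events and catheter malfunction descriptively within the intervention arm, without an odds ratio.
4. Report the number missing per endpoint by arm, and say explicitly that outcomes of patients without pancreatoduodenectomy are not filled in as events.

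The cost is a few sentences in the plan and a little extra programming. Trial conduct, data collection and sample size do not change.

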### Data management

All data will be handled confidentially. Access to patient records will be limited to the study group. Patients will be pseudonymized by study identification numbers, and all data will be handled without using names or personal social security numbers. Some of the source data will be stored in a dedicated and secured area at Oslo University Hospital. Data will be stored in a de-identified manner, where each study participant is recognizable by his/her unique trial patient number. A username and password-protected web-based eCRF is generated for each participant (Viedoc™, PCG Solutions, [name]). The data will be stored for 5 years after the final report on the research project has been sent to the ethical committee. Permission for the database has been submitted to Oslo University Hospital, and a description of the database has been provided.

### Interim analyses

The MINIMUM study is not blinded. Consequently, the researches will follow each patient carefully regarding complications. Therefore, the interim analysis will analyze only safety data. An interim analysis will be performed after 50% of the patients have ended the 30-days follow-up visit. Data to be included within the interim analyses are:
Hemorrhage with hemodynamic affection (development of circulatory shock or need of transfusion)InfectionsDeaths; all-cause mortality

Interim analysis is performed by the statistician allocated to this study accompanied by Project Manager/Coordinating Investigator and Academic responsible and supervisor in the MINIMUM study.

### Criteria for premature termination of a patient’s participation in the trial

Consent withdrawal or in the case of the surgery ending without a pancreatoduodenectomy being performed will be considered a termination of the patient’s participation in MINIMUM. A malfunction of the microdialysis catheter or analysis equipment will make it impossible to achieve further adequate microdialysis data. The patients will be followed until discharge and follow-up appointments at 30th and 90th POD, irrespective of a malfunctioning catheter or not.

### Criteria for termination of the clinical investigation

The study may be terminated by the Research responsible representative or the Project Manager/Coordinating Investigator at any time. However, scheduled follow-up, as described in Assessment Schedule, should be continued for all patients who were treated prior to termination of the study. The clinical investigation may be discontinued at the discretion of the Project Manager/Coordinating Investigator, the supervisor, or the Research responsible representative in the event of any of the following:
Occurrence of adverse events unknown to date in respect of their nature, severity, and durationMedical or ethical reasons affecting the continued performance of the trialBy the interim analysis group assessmentDifficulties in the recruitment of patients which makes it impossible to include enough patients in an adequate time period.Cancelation/cessation of microdialysis catheter production which makes it impossible to acquire catheters.

The Research responsible representative and Project Manager/Coordinating Investigator will inform all investigators, local hospital authority, and the ethics committee of the termination of the trial along with the reasons for such action. If the study is terminated early on grounds of safety, the ethics committee will be informed within 15 days.

## Reporting adverse events

Adverse events will be reported in the local “Adverse Event Reporting system” at the including center and will be recorded in the eCRF. The adverse event report will follow standard assessment and management given at Oslo university hospital, i.e. an adverse event note will be posted by the investigator in the hospitals’ own quality system software (Achilles, CGI Norge AS, Oslo, Norway). Thereafter, experts will assess the incident, obtain additional expertise if necessary, and then perform changes (if applicable) in the hospital’s system for the purpose to avoid any later similar incidents. Additionally, any adverse event will be documented in the patient’s medical record and reported to the Project Manager/Coordinating Investigator by the principal investigator. The Project Manager/Coordinating Investigator and the principal investigator will then discuss whether the adverse event could have led to a serious adverse event. In case of disagreement between Project Manager/Coordinating Investigator and the principal investigator, the Project Manager / Coordinating Investigator shall communicate both opinions to the Research responsible The protocol may require representative, catheter manufacturer, and the ethics committee.

## Protocol amendments

The protocol may require amendments during the conduct of a clinical investigation. Any amendment to the protocol will be agreed upon between the Project Manager / Coordinating Investigator and the principal investigator. The amendments will be notified (in the case of non-substantial amendments) to, or approved by (in the case of substantial amendments) the ethics committee and local authority.

## Deviations from protocol

By signing the protocol, the investigator confirms that the clinical investigation will be performed in accordance with the protocol. A disqualification of an investigator or principal investigator from the clinical investigation may be applicable if mismanagement and neglect of following this protocol persist despite several feedbacks given by the Project Manager/Coordinating Investigator/Research responsible representative.

## Ethical considerations

All patients will follow standard surgical procedure at the site. The only addition is placing a microdialysis catheter near the anastomosis during the end of surgery in half of the patients. Sampling dialysate from the catheter is not associated with any discomfort. Blood samples will not be timewise in excess of routine blood testing. Project Manager / Coordinating Investigator and Research responsible representative will monitor/follow drop-outs, protocol deviations and perform a safety interim-analysis after 50% of patients have finished the study period. This means that if microdialysis method used in clinical assessments are particularly beneficial or harmful compared to the control group while the study is on-going, the Project Manager/Coordinating Investigator and Research responsible representative may consider termination of the study earlier than planned.

All patients with a microdialysis catheter and microdialysate value of glycerol ≥ 400 μmol/L in three consecutive samples will have an abdominal CT scan on POD 2. The radiation dose associated with this examination is considered negligible.

## Discussion

Pancreatic surgery is the only curative modality for pancreatic neoplasm. Despite better surgical techniques and improvement in postoperative care, the morbidity and mortality are still high. For the most part the morbidity is due to postoperative pancreatic fistula, which is regarded as the most threatening complication after pancreatic resection. This risk is also present for other diseases where a pancreatoduodenectomy is performed. Developing a POPF in a patient may have a great influence for the patient considering increased morbidity and mortality, but also may have a big impact for the hospital and the financial burden to the society. Diagnosing a POPF is traditionally based on clinical assessment together with blood samples and CT scans. These diagnostic tools reveal a POPF relatively late in the course of the natural development of this complication which may account for the high observed morbidity and mortality. Also, in a pancreatoduodenectomy an abdominal drain is inserted at the end of surgery and is commonly removed on POD 3. This can be a disadvantage in terms of fast mobilization after surgery. Using the microdialysis method the investigators are hoping to reveal a POPF at an earlier stage thereby initiate earlier interventions. Also, if microdialysis at POD 1 reveals no suspicion of a POPF, the abdominal drain is removed the POD 1, allowing for early mobilization. This in turn may reduce LOS at the hospital, morbidity, and mortality.

Therefore, the current trial will focus on generating information of how microdialysis results may impact the postoperative course after pancreatoduodenectomy. Both morbidity, LOS, costs, and any adverse effects will be assessed. Blinding of the study is not possible. The group affiliation is obvious for the different caregivers and the patients. Another limitation is that this study is a single-center study, potentially reducing the generalizability. As far as we know, this is the first randomized, controlled study to compare microdialysis versus standard of care in patients undergoing pancreatoduodenectomy. The study findings could improve the future treatment of patients undergoing pancreatoduodenectomy. Intraabdominal microdialysis could potentially improve the postoperative course reducing morbidity and mortality. Furthermore, there is a great potential for shortening ICU and hospital length of stay, and considerably reducing the cost for this group of patients. This study may open the possibility for using microdialysis as standard monitoring in patients undergoing pancreatoduodenectomy. Also, information about the patient course until 90 days postoperatively may reveal both short- and long-term follow-up knowledge. We are planning to publish our results in international peer-review journals and authorship will be awarded according to Vancouver convention.

